## Methods

### Data collection

#### A. HbA1c

This will be collected in two ways because of problems with standardisation.

1. Venepuncture at baseline and 12 months and 24 months post recruitment: For the primary outcome, HbA1c will be collected by venepuncture (by a skilled local clinician) and transported to a single laboratory (University College Hospital) for analysis. This will ensure direct comparability of results from all clinics.

2. Routine clinical measurement of HbA1c (secondary outcomes): It is standard practice to measure HbA1c 3 monthly and the researchers will assist the clinic staff in ensuring that these data are obtained and recorded for all participants at 3 and 6 months post recruitment. Values from the different clinics will be standardised to DCCT aligned values using an accepted approach.

#### B. Questionnaires

A range of diabetic, economic, psychosocial and quality of life data will be collected at baseline and 12 and 24 months post recruitment using standardised questionnaires. Participants, parents and clinic staff as appropriate will complete questionnaires in clinic. Researchers will provide support where necessary.

#### C. Economic data

In addition to HbA1c and questionnaire data on service use, data on costs of the intervention will be carefully recorded by researchers and clinic staff.

#### D. Process evaluation data

Qualitative and quantitative data will be collected through i) observation of training of clinic staff and delivery of intervention sessions with young people and parents ii) focus groups with young people and parents iii) interviews with trainers, clinic staff delivering sessions to young people and other stakeholders iv) structured questionnaires with young people and clinic staff. Trained researchers who have extensive experience of working with young people and other staff and who have no involvement in the design or delivery of the intervention will carry out all data collection.

### Proposed type and frequency of data analysis

#### Quantitative data analysis

HbA1c data and other quantitative data from structured questionnaires will be analysed using STATA (StataCorp, Statistical Software: Release 10.0. 2005, Stata Corporation: College Station, TX.). All primary analyses will be carried out according to the principle of intention-to-treat and taking into account the clustering. Every effort will be made to obtain outcome measures on participants, even if some drop out during the course of the group sessions. The data will be analysed by multiple regression modelling, fitting baseline measures of outcomes as covariates. The small groups in which experimental and control interventions are delivered will be fitted as a random effect. A small number of secondary analyses based on explicit hypotheses, such as subgroup and explanatory analyses considering compliance with the interventions, will be specified in advance. Interim analyses will be reported in confidence to the independent Data Monitoring Committee.

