### Randomisation

As this is a cluster randomised trial, clinics will be randomised to intervention or control groups. Randomisation will be minimised by factors likely to influence clinic mean HbA1c; e.g. clinic age (paediatric or adolescent) and the degree of clinic specialisation (district general hospital clinic or teaching hospital/tertiary clinic).

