### Sample size calculation

The standard deviation (SD) of HbA1c in the target population is approximately 1.5%. We propose to recruit sufficient young people to allow the trial to detect a difference between groups of 0.5 standard deviations, i.e. 0.75%, with 90% power at a significance level of 0.05 (2-tailed); this is considered to represent a moderate size of effect. This is a highly clinically meaningful effect, given that the Diabetes Control and Complications Trial showed conclusively that a reduction of approximately 1.5% in HbA1c reduced the risk of microvascular complications in adults by 40% (microalbuminuria) to 75% (retinopathy) over 6.5 years,.[3] with similar benefits seen in adolescents.[28] There is considerable other evidence that smaller reductions in HbA1c, of the order of 0.5% are clinically highly significant, e.g. the DCCT found a continuous association of higher HbA1c and greater microvascular risk.[3] The DAFNE trial in adults had an effect size of approximately 1% reduction in HbA1c.[11] Additionally, a reduction of 0.5 SD is half the effect size identified in our pilot work (1.0 SD). Our power calculations are based upon an intracluster correlation coefficient (ICC: the variability in outcome between clinics divided by the sum of the within-cluster and between-cluster variabilities) of 0.1. In the absence of reliable data on which to calculate an ICC for the clinic population, this has been chosen to be compatible with ICCs calculated from the Northern Irish.[29] and Scottish audits,.[30] and databases of ICCs such as . With these assumptions, 13 clinics in each arm with an average of 20 young people in each would be required to detect a difference of half a standard deviation (0.75) with over 90% statistical power at 5% significance. Given the possible loss to follow up of approximately 10%, the target recruitment will be inflated to 22 young people from each clinic. This is in line with the expected 25% anticipated recruitment rate as experienced in our previous intervention study.

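### The analysis model names baseline outcome but none of the clinic-level minimisation factors as covariates; fitting those factors would guard against over-wide intervals at almost no cost

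*Protocol article*

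**What the plan says.** Under Randomisation, the protocol article states: "Randomisation will be minimised by factors likely to influence clinic mean HbA1c; e.g. clinic age (paediatric or adolescent) and the degree of clinic specialisation". The two factors are offered as examples, so the final list is not fixed there. The stated reason for choosing them is their expected link with the primary outcome at clinic level.

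Under Quantitative data analysis, three sentences describe the model:

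- On the analysis principle: "All primary analyses will be carried out according to the principle of intention-to-treat and taking into account the clustering". The level of clustering is not named.
- On covariates: "The data will be analysed by multiple regression modelling, fitting baseline measures of outcomes as covariates". No other sentence deals with adjustment.
- On random effects, the article names one: "The small groups in which experimental and control interventions are delivered will be fitted as a random effect".

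The article nowhere says that the minimisation factors enter the model. It also nowhere says that baseline is the only covariate or that the factors are excluded.

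**The concern.** Minimisation makes the arms alike on the chosen factors. Whatever those factors contribute to clinic mean HbA1c then largely cancels from the treatment difference. A model without them still counts that contribution as unexplained clinic variance, so the reported standard error is larger than the true sampling error of the difference. The interval is too wide and the test rejects too rarely under the null.

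Clinic variance is the component that matters most in this design. With an ICC of 0.1 and 20 young people per clinic, it makes up 0.1 of 0.145, or 69%, of the variance of a clinic mean before baseline adjustment. The width of the HbA1c interval also matters beyond the primary test, because the article's economic model takes the trial's HbA1c effect as an input and examines uncertainty by probabilistic sensitivity analysis.

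**Working it through.** **Inputs from the protocol article (Sample size calculation).** SD 1.5; difference 0.75, which is 0.5 SD; two-sided 5%; ICC 0.1; 13 clinics per arm; an average of 20 analysed per clinic.

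**Inputs assumed, because the article gives none.** The share R² of between-clinic variance explained by the minimisation factors: 0 to 0.5. Baseline-to-outcome correlations: 0.5 or 0.7 within clinic and 0.7 or 0.9 between clinics. The factors are taken as balanced between arms and clinic as a level in the model.

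**Step 1: the article's own power.** Design effect = 1 + (20 − 1) × 0.1 = 2.9. Effective number per arm = 260 / 2.9 = 89.66. SE = 1.5 × √(2 / 89.66) = 0.224. Power = Φ(0.75 / 0.224 − 1.96) = 0.917. This reproduces the stated figure of over 90%. A t test on clinic means with 24 degrees of freedom gives 0.895.

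**Step 2: omitting the factors, before baseline adjustment.** In SD² units, the clinic-mean variance is 0.1 + 0.9/20 = 0.145. With balanced factors, the variance that actually drives the difference is 0.1 × (1 − R²) + 0.045. The excess width is √(0.145 / that value) − 1. For R² = 0.25 this is √(0.145 / 0.120) − 1 = 9.9%.

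| R² | Excess width | Type I error | Power without factors | Power with factors |
|---|---|---|---|---|
| 0 | 0% | 0.050 | 0.917 | 0.917 |
| 0.10 | 3.6% | 0.042 | 0.925 | 0.934 |
| 0.25 | 9.9% | 0.031 | 0.936 | 0.957 |
| 0.50 | 23.5% | 0.016 | 0.957 | 0.985 |

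These are normal approximations. Simulating 40,000 trials of 26 clinic means with t tests gave power without and with the factors of 0.901 and 0.913, 0.912 and 0.940, and 0.931 and 0.978 for R² of 0.10, 0.25 and 0.50.

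**Step 3: with baseline fitted, as the article plans.** Between-clinic variance becomes 0.1 × (1 − r_c²) and the within-clinic part becomes 0.045 × (1 − r_w²), where r_c and r_w are the clinic-level and within-clinic correlations. R² now means the share of the remaining clinic variance. Lower end: r_w = 0.5, r_c = 0.9, R² = 0.10 gives √((0.019 + 0.03375) / (0.0171 + 0.03375)) − 1 = 1.9%. Upper end: r_w = r_c = 0.7, R² = 0.50 gives √((0.051 + 0.02295) / (0.0255 + 0.02295)) − 1 = 23.5%.

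| r_w, r_c | R² 0.10 | R² 0.25 | R² 0.50 |
|---|---|---|---|
| 0.5, 0.7 | 3.2% | 8.5% | 19.6% |
| 0.5, 0.9 | 1.9% | 4.8% | 10.4% |
| 0.7, 0.7 | 3.6% | 9.9% | 23.5% |
| 0.7, 0.9 | 2.3% | 6.2% | 13.7% |

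Type I error across these cells runs from 0.016 to 0.046. Power for 0.75% exceeds 0.99 in every cell with or without the factors. The largest difference is 0.9957 against 0.9974, about 0.2 points. If baseline HbA1c absorbs the factors entirely, R² is 0 and there is no excess width.

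**Step 4: the price of fitting them.** Two binary factors take the clinic-level degrees of freedom from 26 − 2 = 24 to 26 − 4 = 22. If they explain nothing, t-based power before baseline adjustment goes from 0.895 to 0.892 (simulated: 0.896 to 0.894).

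**The case against.** The strongest reply is that this is a condensed article and a complete covariate list may stand in a full protocol or SAP that is not shown. A reader might infer that the factors have been deliberately excluded; the text does not support that, since it neither says so nor calls baseline the sole covariate. What remains is that the article does set out a specific model, with covariates and a random effect, and the factors used for allocation are not in it. Fitting them is a concrete improvement on the model as published.

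A second reply is that baseline HbA1c measures directly what the factors were chosen to predict, so it may leave them little to explain. That is fair, and it is why the harm can be zero. It need not be: the Background links poor control particularly to the developmental changes of adolescence, so clinic age group could plausibly predict the course over 12 to 24 months beyond baseline.

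A reader might also take the power differences in Step 2 as the trial's loss. They describe an analysis without the baseline covariate, which is not what is planned. Even there, the loss is only relative to the adjusted model: where the factors matter, power without them is 0.925 to 0.957 (0.901 to 0.931 simulated), not below the planned level.

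Finally, the direction depends on clinic being modelled. The only random effect named is the small group. If clinic were left out, intervals could be too narrow: with groups of 4, the design effect would be 1 + 3 × 0.1 = 1.3 instead of 2.9, and the SE √(1.3 / 2.9) = 0.67 of the correct one. The article does commit to allowing for clustering, so this is a condition on the present point and a separate matter to settle.

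**Conclusion.** The point holds as a conditional one. Allocation uses factors selected for their expected link with HbA1c, and the published model names none of them. If they predict outcome beyond baseline and clinic-level clustering is modelled, the primary analysis will be conservative, with intervals about 2% to 24% too wide. That range rests on the assumed correlations and on an assumed 10% to 50% of remaining clinic variance explained; the article supplies neither. The excess is zero if baseline absorbs the factors.

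There is no inflation of false positives by this route, no breach of the planned 90% power, and a negligible power loss for 0.75% once baseline is fitted. Certain or substantial lost power cannot be concluded from the document. The gain from adjustment is chiefly a correctly sized interval.

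**What to change.** Amend the covariate sentence under Quantitative data analysis so that the primary HbA1c model fits the baseline measure of the outcome together with every clinic-level factor actually used in the minimisation. Name those factors in final form, since the Randomisation section gives clinic age group and specialisation only as examples.

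The cost is one line of text and, for two binary factors, about two of 24 clinic-level degrees of freedom. That is roughly 0.2 to 0.3 points of power if the factors turn out to explain nothing. The sample size of 26 clinics and 572 participants does not change.

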**Methods/Design:**

The CASCADE trial is a multi-centre randomised control trial with 26 clinics randomised to control or intervention groups, with 572 children and young people involved in the study. The intervention will be delivered in 4 group sessions, over a 4 month period. A developmentally appropriate curriculum will be delivered to groups of 3 - 4 families, focusing on achievement of increasing competency in self-management of diabetes. The control group will receive standard care from their clinical team, usually consisting of regular 3-monthly clinic visits and telephone contact as required with the clinical nurse specialist and consultant. The primary outcomes of the trial will be change in HbA1c between baseline and 12 months and 24 months post recruitment. Secondary outcomes will include measures related to the economic evaluation, psychosocial outcomes, outcomes related to management of diabetes outcomes, and adherence to the intervention.

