### Interventions - control group

Control families will continue to receive the usual standard care.[26] from their NHS clinical team, this usually consists of regular 3-monthly medical clinic visits plus telephone contact as required with the clinical nurse specialist and consultant. The process evaluation will monitor and describe standard care as well as the CASCADE intervention.

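### The only random effect the analysis names is the small session group, not the randomised clinic, and control families have no such groups; if it is the only clustering term, the primary test is anti-conservative

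*Protocol article*

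**What the plan says.** The Randomisation section of the protocol article fixes the unit: "As this is a cluster randomised trial, clinics will be randomised to intervention or control groups". The Sample size calculation section uses the same unit. It takes an ICC of 0.1, defined as "the variability in outcome between clinics divided by the sum of the within-cluster and between-cluster variabilities", with 13 clinics per arm and 20 young people analysed per clinic.

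The Quantitative data analysis section makes two statements about clustering. The first is general: "All primary analyses will be carried out according to the principle of intention-to-treat and taking into account the clustering". It names neither the level nor the method. The second gives a method: "The small groups in which experimental and control interventions are delivered will be fitted as a random effect". Clinic is not named as a model term anywhere in that section.

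Small groups are described for one arm only. The abstract says of the intervention: "A developmentally appropriate curriculum will be delivered to groups of 3 - 4 families". The section on the control group says "Control families will continue to receive the usual standard care", and adds that "this usually consists of regular 3-monthly medical clinic visits plus telephone contact as required with the clinical nurse specialist and consultant". No control session groups are described.

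**The concern.** The one clustering term that is spelled out does not match the randomisation, the sample size or the control arm.

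- **Level.** A clinic contributes about 20 young people, or five groups of four. A model with a session-group effect and no clinic effect treats those five groups as independent, although they share the clinic that was randomised.
- **Control arm.** Control care as described has no small groups, so an analyst would have to invent a coding, and the choice changes the standard error.

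At stake is the comparison of HbA1c between arms. If between-clinic variation is not carried into the standard error, chance differences among 26 clinics can be declared an effect of CASCADE too often, and the confidence interval is too narrow.

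**Working it through.** **Inputs.** From the Sample size calculation section: SD 1.5%, difference 0.75% (0.5 SD), two-sided 5%, clinic ICC 0.1, 13 clinics per arm, 20 analysed per clinic. From the abstract: groups of 3 to 4 families. Assumed: equal clinic sizes, groups of 4 unless stated otherwise, and no variance at session-group level beyond the clinic (relaxed below). Variances are in SD² units.

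**The plan's own figure.** The design effect is 1 + 19 × 0.1 = 2.9, so the effective sample is 260/2.9 = 89.7 per arm. Then 0.5/√(2/89.7) = 3.35, and 3.35 − 1.96 = 1.39, which gives power of 91.7%. This agrees with the stated power of over 90%, with the clinic as the cluster.

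**Correct variance of an arm mean.** (0.1 + 0.9/20)/13 = 0.01115. The SE of the difference is √(2 × 0.01115) = 0.149 SD, or 0.224% HbA1c.

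**Session group as the only term, groups of 4 in both arms (65 per arm).** (0.1 + 0.9/4)/65 = 0.0050. The SE is √(2 × 0.0050) = 0.100 SD, or 0.150% HbA1c. The ratio to the correct SE is √(0.0050/0.01115) = 0.67. Type I error is 2 × [1 − Φ(1.96 × 0.67)] = 19%. With groups of 3 the ratio is √(1.2/2.9) = 0.64 and the error 21%.

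**Session group as the only term, control families as individuals.** The control variance is 1/260 = 0.00385. The SE is √(0.0050 + 0.00385) = 0.094 SD, the ratio 0.63 and the error 22%.

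**Simulation at ICC 0.1.** 2,000 null trials, 26 clinics of 20, REML random intercept:

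| Random effect fitted | Mean model SE (true sampling SD 0.151) | Type I error, z | Type I error, t on 24 df |
|---|---|---|---|
| Groups of 4 in both arms | 0.099 | 19.8% | 17.8% |
| Groups of 4; controls as individuals | 0.093 | 21.8% | 20.0% |
| Groups of 4; each control clinic as one group | 0.125 | 11.7% | 10.0% |
| Clinic | 0.148 | 6.0% | 5.4% |

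Under the third coding the SE is 0.125/0.151 = 0.83 of the true value, so it is about one sixth too small, not one third.

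**Added session-group variance.** Putting an extra 0.05 of variance at session-group level in the CASCADE arm changes little. The three group-only codings give 19.3%, 21.9% and 9.2% (z), and the clinic random effect alone gives 6.8% (z) or 5.2% (t). It is the clinic term that controls the error.

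**Lower residual ICC.** The simulation omits the baseline covariate, which may lower the clinic ICC that remains. Type I error (z reference) for groups of 4 in both arms, then for controls as individuals:

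- ICC 0.05: the correct variance is (0.05 + 0.95/20)/13 = 0.00750 and the group-only variance (0.05 + 0.95/4)/65 = 0.00442. The error is 13% and 15% by formula, 12.2% and 12.8% simulated.
- ICC 0.02: the correct variance is (0.02 + 0.98/20)/13 = 0.00531 and the group-only variance (0.02 + 0.98/4)/65 = 0.00408. The error is about 8-9% by formula.
- ICC 0.01: 6.2% and 6.5% simulated.

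**The case against.** The strongest reply is that the same section has already committed the primary analyses to account for clustering. In this document the cluster is the clinic: the design, the randomisation and the ICC definition all say so. On that reading the small-group term is an addition, for correlation among families taught together, and nothing says that clinic is omitted. The text is also a journal article. How levels nest and which degrees of freedom are used are commonly left to the full protocol or the analysis plan, neither of which is shown. Finally, the ICC of 0.1 was chosen without reliable data, and baseline adjustment may reduce it.

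Much of this stands. A reader might infer that the primary standard error will be too small, but the documents do not support that as a flat statement, because the general commitment can cover a clinic-level adjustment. Nor is the missing degrees-of-freedom rule a fault here. The text misstates nothing on that point, and with a clinic effect the choice moves the error only between about 5% and 6%.

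The reply does not remove the point. The general clause gives no level or method, and the only sentence that gives a method names a level other than the randomised one. That sentence also refers to control groups that the design does not have. This is a wrong statement in the text, not a detail left for later.

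**Conclusion.** The point holds in conditional form. The analysis section is ambiguous about the clustering level, and it contradicts the control arm, where its named random effect cannot be fitted as written.

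If the session group is the only clustering term, then at the plan's clinic ICC of 0.1 the SE is about one third too small with controls coded in fours or as individuals. The two-sided type I error is about 12% to 22% across the three control codings (z reference). With a lower residual ICC it is about 12-15% at 0.05 and 8-9% at 0.02, for controls in fours or as individuals. The error was above nominal in every group-only case with a z reference, but close to it when the ICC is very small.

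These figures assume 13 clinics of 20 per arm, equal sizes and no clinic-level adjustment elsewhere in the model. They show what the literal model would do. They are not evidence that it will be fitted.

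**What to change.** Replace the small-group sentence in the Quantitative data analysis section with text to this effect:

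> Clinic, the unit of randomisation, will be fitted as a random effect in both arms (or an equivalent clinic-level adjustment will be used), preferably with a small-sample reference distribution. In the intervention arm only, CASCADE session group will be a further random effect nested within clinic.

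Delete the reference to small groups for control families. If the analysis plan already specifies a clinic term, the published wording should be brought into line with it.

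The change is to wording only and needs no further participants, visits or data. Compared with a group-only model, the confidence interval becomes wider. At ICC 0.1 and groups of 4, its half-width goes from 1.96 × 0.150 = 0.29% to 1.96 × 0.224 = 0.44% HbA1c. The wider interval is the correct one and matches the basis on which the trial was powered.

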#### Qualitative data analysis

Data from observations, interviews and focus groups as well as open-ended questionnaire responses will be analysed using a system of coding and memoing developed by Lofland and Lofland (1995),.[31] facilitated by the use of NVivo software. First, the key topics and issues that emerged from the data will be identified through familiarisation with transcripts or documents. Pertinent excerpts that illustrate emerging themes will be coded and memos written to summarise and synthesise these emerging themes. In an iterative process, researchers will refine their analysis, ensuring that the themes built up are cross-checked with other data. To maximise the validity of our findings, two researchers will separately analyse a sample of the qualitative data and then meet to compare their analyses and agree a framework for full analysis of all data.

